## Abstract

**Highlights:**

By the age of 65 the cumulative incidence of dementia exceeds 90% in adults with DS.There is a paucity of non‐pharmacological interventions to delay AD in adults with DS.Clinical trials in adults without DS suggest that intentional weight loss may improve cognitive function and reduce the risk of developing AD.A randomized trial exploring the impact of weight loss on AD biomarkers in adults with DS is currently underway.This trial will explore if non‐pharmacological approaches could delay onset of AD in adults with DS.

## INTRODUCTION

1

Down syndrome (DS), or trisomy 21, is the most common chromosomal abnormality associated with an intellectual disability (ID).^1^ Most adults with DS will develop pathology related with Alzheimer's disease (AD).^2^ The median age of dementia onset is 53.8 years,^3^ and the lifetime incidence is 90%.^2^ High rates of AD in DS are the result of the overproduction of amyloid‐beta (Aβ) from the additional copy of the amyloid precursor protein found on chromosome 21. Aβ accelerates neurodegeneration, oxidative stress, plaque deposition, and early development of AD‐like pathology in individuals with DS.^4^ Research suggests that deposition of Aβ occurs decades earlier in adults with DS compared with typically developed adults, with a mean age of AD onset of 53.8 years. However, a recent review found significant individual variability in onset (25 years),^5^ suggesting that the risk and timing of dementia is modifiable. Lifestyle factors are posited to explain part of this variability. In adults without DS, lifestyle factors contribute to 45% of late onset AD.^6^

Evidence from both epidemiological and clinical observations suggest that in the general population, mid‐life obesity is a significant risk factor for later‐life dementia (including AD) independent of comorbidities such as hypertension and diabetes.^6^ However, the impact of obesity on AD risk in adults with DS remains largely unexplored. To our knowledge, only one study has examined this relationship, finding an association between body mass index (BMI) and Free and Cued Recall in 66 adults with DS without dementia.^7^ Given the high prevalence of obesity in adults with DS (∼81%)^8^ further research is needed to better understand its role in AD risk and progression in this population.

Similarly, the available data from trials in typically developed adults suggest the potential for weight loss achieved through a reduced energy diet and/or consuming a low glycemic load, low saturated fat, high fruit and vegetable diet to prevent or delay the development of AD.^9^, ^10^, ^11^, ^12^ Additionally, in adults without DS, the Mediterranean‐DASH diet Intervention for Neurodegenerative Delay (MIND) dietary pattern is associated with improved cognitive function and reduced incidence of AD.^13^, ^14^, ^15^ However, the potential of weight loss and dietary interventions to prevent or delay AD in mid‐life adults with DS has not been previously examined.

Our group has developed a multi‐component intervention, including a reduced energy‐enhanced Stop Light Diet (eSLD), individual behavioral counseling/education, self‐monitoring, and promotion of physical activity, which has been shown to achieve and sustain clinically relevant weight loss (≥5%) and improvements in diet quality in adults with ID. The eSLD includes daily consumption of two portion‐controlled entrées (∼200 kcal each), two low‐calorie/high protein shakes (∼100 kcal each), a minimum of five servings of fruits/vegetables, and ad libitum noncaloric beverages. Participants are asked to select additional low energy food, if desired, using the SLD system: green (low energy), yellow (moderate energy), and red (high energy). Results from three completed trials which have included a total of 335 adults with ID including DS, have demonstrated improved diet quality and clinically relevant weight loss at both 6 months (−6.2) and 12 months (−6.8%) using the eSLD.^16^, ^17^, ^18^ This article provides the methods and rationale for a randomized trial that will use the eSLD to evaluate the impact of weight loss and dietary intake on factors that may prevent or delay the development of AD in adults with DS.

## METHODS

2

### Overview of study design

2.1

This is a 12‐month randomized trial in 81 non‐demented adults with DS. Participants will be randomized (2:1) to either a weight loss or a general health education control group. The weight loss arm will follow the protocol used in our previous trials,^16^, ^17^, ^18^ plus recommendations from the MIND diet,^13^, ^14^ to increase antioxidant consumption and further improve diet quality. Participants and a study partner will be asked to attend monthly behavioral counseling/education sessions with a trained interventionist delivered remotely using Zoom video conferencing (San Jose, CA, USA) and self‐monitor diet and body weight using commercially available Web‐based applications. Participants and a study partner in the control arm will be asked to attend monthly behavioral counseling/education sessions with a trained interventionist delivered remotely and will receive education on general health education topics such as injury prevention, oral health, sleep, hydration, exercise and physical activity, and healthy eating. Outcomes assessed across 12 months will include (1) biomarkers related to AD including plasma amyloid beta 42:40 ratio (Aβ 42/40), phosphorylated Tau (pTau217), neurofilament light (NfL), and glial fibrillary acidic protein (GFAP); (2) cognitive function using both directly‐administered and informant‐based assessments; (3) cardiometabolic biomarkers such as lipid levels, blood glucose levels, and inflammatory markers; (4) cerebral antioxidants and brain volume assessed by magnetic resonance spectroscopy; and (5) dietary intake assessed using 3‐day photo‐assisted food record and skin carotenoid content using a Veggie Meter. Our analysis will include three aims (Table 1). This trial will provide preliminary data on the impact of weight loss and improved diet quality on cognitive function and factors associated with the development of AD.

**TABLE 1 alz70219-tbl-0001:** Study aims for a 12‐month weight loss intervention in adults with Down syndrome.

Aim 1	Calculate effect sizes for changes in plasma biomarkers related to AD, cardiometabolic biomarkers, and cognitive function in both intervention arms across 12 months.
Aim 2	Calculate effect sizes for changes in cerebral antioxidants and brain volume in a subsample of participants in both intervention arms across 12 months.
Aim 3	Explore the independent effects of weight loss or diet quality on changes in plasma biomarkers related to AD, cerebral antioxidants and brain volume, and cognitive function across 12 months.

Abbreviation: AD, Alzheimer's disease.

### Participant eligibility

2.2

To enhance generalizability, individuals with DS on medications for common chronic diseases (i.e., depression, hypertension, type 2 diabetes), using dietary supplements, or consuming a gluten‐free diet (i.e., celiac disease) will not be excluded. Random assignment should distribute these characteristics equally across interventions arms. Additionally, we will control for baseline characteristics in our analysis. Inclusion and exclusion criteria are provided in Table 2.

**TABLE 2 alz70219-tbl-0002:** Participant eligibility criteria for a 12‐month weight loss intervention in adults with Down syndrome.

Inclusion	
Residential status	Living at home with a parent/guardian or in a supported living environment with a family member, caregiver, or direct support professional who agrees to serve as a study partner for the entire 12‐month intervention
Age	18–64 years
Diagnosis	Down syndrome
BMI	25–50 kg/m^2^
Communication	Sufficient functional ability to understand directions, communicate preferences, wants, and needs through spoken language
Exclusion	
Dementia	Diagnosis of dementia as determined by the Dementia Screening Questionnaire for Individuals with Intellectual Disabilities (DSQIID)
Health concerns	Serious medical risk (e.g., recent cancer, recent heart attack, stroke, pregnancy, angioplasty) as determined by the health history form Insulin‐dependent diabetes Dairy allergy Swallowing disorders that require a thickened liquid diet
Medications	Individuals on GLP‐1 antagonist Individuals taking warfarin or other blood thinner medications Individuals taking anti‐amyloid medications or other medications related to the treatment of Alzheimer's disease
Other	Participation in a weight management program involving diet and PA in the past 6 months Unwilling to be randomized

Abbreviations: BMI, body mass index; GLP‐1, glucagon‐like peptide‐1; PA, physical activity.

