#### Analysis

2.9.2

We will assess plasma biomarkers related to AD, cardiometabolic biomarkers, cognitive function, energy and macronutrient intake, and diet quality at baseline, 6 and 12 months. We will assess cerebral antioxidants and brain volume at baseline and 12 months. We will calculate the mean, standard deviation, and 95% confidence intervals in both the intervention and control arms for each of these outcome variables at each time point, and for the change from baseline to each time point. This descriptive information will be summarized graphically which will aid in determining if, and when, differences in outcome variables arise among and across the two arms. Linear mixed models with an autoregressive correlation structure and a random intercept for each participant will be used to model the longitudinal serial correlation and baseline between‐subject variation. The model will include a main effect for intervention arm, and time and an arm‐by‐time interaction. The point estimate and 95% confidence interval for the arm‐by‐time interaction evaluated at both 6 and 12 months will be used to estimate the between arm effect size. Mixed models will be adjusted for age, sex, ethnicity/race, MVPA, premorbid ID, number of study participants living in the same household, intervention attendance, and intervention arm. Model fit will be assessed using diagnostic plots and comparing likelihood values between alternative model formulations or transformations, when appropriate. No multiplicity adjustment will be conducted since no hypotheses will be tested.

To determine the independent effects of weight loss or diet quality on changes in plasma biomarkers related to AD (Aβ 42/40, pTau217, and NfL), cerebral antioxidants, brain volume, cardiometabolic biomarkers, and cognitive function we will conduct a set of nested likelihood ratio tests (LRT). The goal of this analysis is to determine if weight loss, diet quality or both should be targeted in future trials for the prevention of AD in adults with DS. No adjustment for multiple testing will be conducted because rejection of any of the nested comparisons will imply that a change in a greater number of underlying covariates, for example, weight loss and diet compared to weight loss alone are needed to elicit changes in biomarkers.

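### Table 2 excludes users of a GLP-1 antagonist, so read literally no criterion excludes users of weight-lowering GLP-1 receptor agonists; the intended drug class needs confirming

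*Protocol article*

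**What the plan says.** Section 2.2 (Participant eligibility) opens with a general statement that "individuals with DS on medications for common chronic diseases (i.e., depression, hypertension, type 2 diabetes), using dietary supplements" and those on a gluten-free diet remain eligible. It adds that randomisation should spread these characteristics over the arms and that baseline characteristics will be controlled for. It then refers to Table 2 for the criteria.

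The first medication exclusion in Table 2 is "Individuals on GLP‐1 antagonist". The others are warfarin and other blood thinners, and anti-amyloid or other Alzheimer's medication. The table's footnote expands the abbreviation as "GLP‐1, glucagon‐like peptide‐1" and says nothing about agonist or antagonist. GLP-1 is mentioned nowhere else in the article.

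Two further exclusions come near the subject: "Insulin‐dependent diabetes" and "Participation in a weight management program involving diet and PA in the past 6 months".

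On the analysis side, Aim 3 in Table 1 is to "Explore the independent effects of weight loss or diet quality on changes in plasma biomarkers related to AD", cerebral antioxidants, brain volume and cognition. Section 2.9.2 adds cardiometabolic biomarkers to the outcomes of that analysis. For covariates it states: "Mixed models will be adjusted for age, sex, ethnicity/race, MVPA, premorbid ID, number of study participants living in the same household", followed by session attendance and allocated arm.

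**The concern.** The exclusion names a class with the opposite action to the one that matters in a weight-loss trial. A rule against antagonists, followed to the letter, leaves agonist users eligible.

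The stake lies chiefly in Aim 3. There the explanatory variable is the weight change a participant actually achieves, not the allocated arm. A participant whose weight falls because of a drug contributes weight loss that neither the diet nor the counselling produced. The drug may also act on glucose and lipids directly, and people who take it for type 2 diabetes differ from the rest in their underlying disease. Each of these could be read as an effect of weight loss. Section 2.3 gives the association of weight loss and dietary change with biomarkers and cognition as the reason for 2:1 allocation, so this is an analysis the design was shaped to serve.

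**Working it through.** No figure in the article can be recomputed here. The check is whether any stated rule excludes an agonist user, and then whether the analysis would deal with one who was admitted.

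**Step 1: the eligibility rules, one by one, for a person on a GLP-1 receptor agonist.**

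| Rule (section 2.2, Table 2) | Does it exclude this person? |
|---|---|
| GLP-1 antagonist | No, opposite class |
| Blood thinners | No |
| Anti-amyloid or other Alzheimer's medication | No |
| Insulin dependence | Only if also insulin-dependent |
| Recent weight management programme | No, it concerns diet and physical activity, not drugs |
| Serious medical risk, dairy allergy, swallowing disorder, dementia, unwillingness to be randomised | No, unrelated to the drug |
| Opening sentence on chronic-disease medication | Points to admission if the drug is taken for type 2 diabetes |

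The inclusion criteria (residence, age, diagnosis, BMI, communication) do not mention medication. Read literally, nothing excludes this person.

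**Step 2: the same text with the word read as agonist.** Table 2 would then exclude a class used for type 2 diabetes, while the opening sentence says that users of medication for that condition are not excluded. This can be read as a general statement followed by listed exceptions, but the article does not say so.

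**Step 3: Aim 3.** Suppose an admitted user's weight change is W = (change due to the intervention) + (change due to the drug), and the outcome change depends on W, on any direct drug effect and on the underlying disease. A model of outcome on W without a term for drug use places the last two in the weight-loss coefficient to the extent that they vary with W. Allocation was randomised but W was not, so randomisation gives no protection. The covariates listed in section 2.9.2 are age, sex, ethnicity/race, MVPA, premorbid ID, household clustering, attendance and arm. Drug use is not among them. The promise in section 2.2 to control for baseline characteristics is general and names no medication term.

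**Step 4: the arm contrast.** Drug use at screening precedes randomisation, so both arms have the same expected proportion of users. If the drug acts similarly in both arms, the contrast has no systematic bias. It gains variance, and chance imbalance is possible: section 2.9.1 plans 27 controls with 20% attrition, and 27 × 0.8 = 21.6, or about 22 control completers.

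**Step 5: size.** If k of n completers in an arm are users and each changes weight by d points because of the drug during the 12 months, that arm's mean moves by k × d / n. The article gives n approximately but neither k nor d. A person already stable on a drug at baseline may have d near zero. The shift therefore cannot be derived, and neither can any resulting shift in NfL or the other outcomes.

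**The case against.** The strongest reply is that this is one wrong word. An exclusion for antagonists would exclude almost nobody, which is itself good evidence that agonist was meant. The document is a journal article; the full protocol and the screening forms are not shown, and staff may already apply the intended rule. All of this stands. It limits the claim to the published criterion and does not make that criterion correct.

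It may also be said that the opening sentence is a general rule to which Table 2 lists exceptions, so that no conflict remains once the word is corrected. That is a reasonable reading, and it makes the type 2 diabetes sentence the lesser part of this point. A short clarification would still spare the screener from having to infer it.

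A reader might go further and infer that agonist users are being enrolled, or that they distort the trial materially. For example, one could assume a drug-related loss of 5 to 15 points per user and place three users among 22 control completers: 3 × 5 / 22 = 0.68 to 3 × 15 / 22 = 2.05 points, against the 6.8% loss at 12 months quoted in the Introduction. The documents do not support this. The per-user loss is an assumption that leaves out values near zero. Under 2:1 allocation, three users among controls would imply about nine in all (3 × 3), and no prevalence is given. Putting every user in one arm ignores randomisation. A shift in mean weight is also not a shift in biomarkers or cognition, which are what Aim 1 estimates.

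**Conclusion.** The point holds in limited form. The published exclusion names the wrong pharmacological class, very probably by a slip, and no other stated criterion makes up for it. If it is applied as written, the Aim 3 weight-loss association is open to confounding by drug use, because randomisation does not protect it and the listed covariates do not address it. For the arm contrasts, the expected consequence is extra noise or chance imbalance, not systematic bias, provided that the drug acts similarly in both arms. The sample size and precision statement, which rests on simulated NfL change, is unaffected.

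The size cannot be stated: it depends on how many users were admitted and how much they changed after baseline. If screening already follows the intended rule, it is nil. The correction is still worth making, since an eligibility rule should not mean the reverse of what was probably intended.

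**What to change.** 1. Confirm which drug class the Table 2 criterion was meant to name, and correct the wording.
2. Reconcile the corrected criterion with the opening sentence of section 2.2 on type 2 diabetes medication, so that the two can be applied together without interpretation. The clinical rule itself is the sponsor's choice.
3. Check the medication histories of participants already enrolled against the corrected wording.
4. If any users were admitted, report a sensitivity analysis of Aim 3 and of the arm contrasts without them. Use at screening is a baseline characteristic, so leaving users out of both arms keeps the comparison among the remaining participants a randomised one.

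The cost is a small change of text and a check of the health histories taken at screening. The design, sample size and main model do not change. Item 4 costs nothing if no users are found.

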### Recruitment/Randomization

2.3

Project staff will contact local community agencies serving adults with DS, case managers, and Community Developmental Disabilities Organizations by mail/email, provide presentations at community agencies and local events, and distribute newsletters describing the project. Interested parents/guardians, caregivers, or adults with DS will be asked to contact the study coordinator via email, our website, or a dedicated toll‐free study phone number that will be included in all recruitment materials. The study coordinator will contact the interested individuals by phone to answer questions and conduct an initial eligibility screen. Video conference visits will be scheduled with those remaining interested, and potentially eligible, to obtain informed consent (participants or legal guardian) and participant assent (if not their own legal guardian) and determine final eligibility based on the DSQIID scores. Participants found to be ineligible will be provided with written materials describing available resources for weight loss. Participants will be stratified by age (18–30 vs. > 30 years) and sequentially computer‐randomized by the study statistician with 2:1 allocation to the weight loss or control arms. This randomization scheme was selected to include more participants in the weight loss arm which will allow for a larger sample size to assess the association of weight loss and changes in dietary intake with changes in biomarkers and cognitive function. Intervention assignments will be concealed and delivered to the study coordinator prior to participant orientation sessions described below.

### Study partner role

2.4

Adults with DS receive assistance from family members and direct support professionals with decisions regarding meal planning, food shopping, and meal preparation, thus, playing an important role in the success of weight loss interventions in this population. For this trial, we will recruit either a parent/guardian, other family member, or direct support professional for those living in group homes to serve as a study partner for each participant. Study partners for participants in both intervention arms will be asked to attend the orientation and all monthly meetings with the interventionist and to provide transportation to our facilities for all outcome assessments. Study partners for participants in the weight loss arm will be asked to support, encourage, and assist participants in complying with the study protocol including the selection and preparation of foods consistent with the dietary recommendations, and assisting participants with self‐monitoring of both dietary intake and body weight.

### Intervention components

2.5

#### Weight loss arm

2.5.1

##### Orientation

Interventionists will conduct two ∼60 min home visits with participants and study partners prior to initiating the intervention. Interventionists will include detailed descriptions of all components of the weight loss intervention protocol. Participants will be provided with an iPad (Apple Inc., Cupertino, CA, USA). All iPads will be pre‐loaded with video conferencing (Zoom) and diet and weight tracking software (CoachCare platform). Participants will receive a tutorial on the use of the iPad, video conferencing and diet tracking software, and wireless scales apps/devices used for self‐monitoring diet and weight.

##### Diet

Reduced energy intake (goal: 1200–1800 kcal/day) will be achieved using an eSLD. Participants will be asked to consume a minimum daily total of two entrées (∼200–300 kcal each, saturated fat ≤ 3 g), one high‐protein shake (∼100 kcal each), five servings of fruits/vegetables, and ad libitum non‐caloric beverages. To increase antioxidant content and improve diet quality, we will incorporate specific recommendations from the MIND diet. Participants and study partners will be trained to use a color‐coded chart that we have developed which categorizes foods based on the Stop Light system to assist in meal planning, grocery shopping, decisions regarding snack foods, and compliance with the diet in special situations such as eating away from home (restaurants, parties, etc.). Participants will be asked to purchase and prepare portion‐controlled entrées from a list meeting the caloric/fat requirements, as well as all fruits and vegetables, and non‐caloric beverages. The study will provide one low‐calorie/high protein, dairy‐based shake per day which will be shipped to the participant's residence monthly.

